## Background

Ninety percent of persons with incident heart failure (HF) are age 65 or over; moreover, the prevalence of HF increases with age, rising from 5-10% in persons aged 65-79 years to 10-20% in those 80 years or over [1]. In Spain, about 500,000 persons over the age of 60 suffer from HF [2]. HF is the most frequent reason for hospital admission and readmission [3] and is the third leading cause of cardiovascular death in the elderly [4]. Moreover, it represents about 2% of total health costs [5]. The number of hospitalisations for HF is expected to increase up to 50% in the next 20 years [6].

HF produces physical and cognitive impairment as well as reduced quality of life [7-9]. Annual mortality exceeds 50% in patients with New York Heart Association (NYHA) classes III and IV [10]. Advanced age, as well as low quality of life and poor social network - two variables which are not routinely assessed in patients - are all associated with a higher risk of hospitalisation and death in HF [11,12].

Treatments are available to modify the course of HF with left ventricular systolic dysfunction (LVSD) [13,14], but they have not managed to significantly reduce mortality and hospital readmission in routine clinical practice [15,16]. The prognosis for HF with preserved systolic function is similar to that of HF with depressed ejection fraction, but there is no evidence of effective treatments in the latter group, and clinical practice guidelines offer few specific recommendations for its treatment. The current therapeutic approach for these patients is symptomatic treatment, together with control of cardiovascular risk factors and heart rate [13,14].

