### Study size

In previous studies we observed that about 30% of HF patients are readmitted every 6 months [11]. These studies were conducted in hospitals and with patient's inclusion criteria different from those in the HF-Geriatrics, and within patients with less use of effective drug treatments than at present. Accordingly, under the conservative assumption that the annual frequency of readmission will be 40%, and that the frequency of readmission is similar in all study hospitals, 700 patients will need to be recruited (350 in each group) to detect, with an alpha error of 5% and a statistical power of 80%, a 20% reduction in hospital admission. This analysis assumes, as can be expected, that no patients will be lost to follow-up. A total of 700 patients also allows to detect, with an alpha error of 5% and 80% power, differences of 10 points (clinically relevant) in the MLWHFQ, assuming that patients in the control group have a mean score of 50 points on this questionnaire [11].

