The main strengths of this study are random assignment to the intervention, concealment of the randomisation list, intention-to-treat analysis, and the very nature of the DMP designed. This DMP follows the recommendations of the major scientific societies in this field (13,14) and has been refined through a literature search for successful interventions. In addition, the intervention will be adapted to the educational level and visual limitations of most patients with the following measures: a) selection of a limited number of self-care skills to manage HF, COPD, diabetes mellitus and depression, to identify the warning signs of decompensation, and to comply with treatment [33]; b) implementation of only two brief educational sessions, the first during hospitalisation and the second on the day of discharge, as well as a telephone call 15 days after discharge; c) development of printed educational materials with brief text and large print, avoiding technical terms and with numerous explanatory pictures, to be given to patients in the intervention group on the day of hospital discharge; d) provision of a telephone contact number to patients so they can ask questions or resolve any issues they may have.

We plan to conduct specific training and certification of the case managers in the coordinating centre and to develop protocols for each of their activities. This ensures that the same intervention will be applied similarly in all participating centres and that, if the efficacy of the DMP is shown, it can easily be expanded to other health care settings.

The main challenges of the project are recruitment of study participants, avoidance of contamination of the intervention between the two trial groups, and minimization of losses to follow-up. To ensure sufficient recruitment, we have reviewed the basic hospital discharge dataset for each participating hospital, and have found that they each admit at least 100 patients with the characteristics needed for the project every 6 months. To avoid contamination, the case manager will conduct the DMP in a separate consultation, at a time of day other than when patients usually receive care. Finally, to minimize losses to follow-up, the intervention will be brief and will include only a small number of hospital visits. In addition, patient access to the case manager will be facilitated (by telephone or in person) so that any questions or problems that arise during the intervention can be addressed.

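### The sample size treats zero loss to follow-up as expected, although the Discussion names losses as a main challenge, and it makes no allowance for deaths before the 12-month MLWHFQ

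*Protocol article*

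**What the plan says.** The Study size section sets two groups of 350 and takes 40% as the yearly readmission rate, which it calls conservative. The target is "a 20% reduction in hospital admission", at 5% alpha and 80% power. The section then adds: "This analysis assumes, as can be expected, that no patients will be lost to follow-up". The same 700 patients are said to give 80% power for a 10-point MLWHFQ difference, with an assumed control mean of 50 and no standard deviation.

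The Discussion names three main challenges: recruitment, contamination, "and minimization of losses to follow-up". Against losses it offers a short intervention, few visits and easy access to the case manager.

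Other sections bear on the point:
- **Study participants:** patients who cannot be followed up are excluded at entry.
- **Description of the intervention:** follow-up ends 12 months after discharge or at death.
- **Study variables and Table 2:** information comes from interview and from clinical records, and deaths are also taken from mortality registries. Mortality is a final outcome.
- **Statistical analysis:** Kaplan-Meier curves for time to readmission or death, hospital-stratified Cox regression, and between-group differences in MLWHFQ change.

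**The concern.** The article is not silent about losses. It affirms that none are expected and makes that a condition of the power statement. A protocol that regards losses as one of its main risks, and designs measures to reduce rather than abolish them, does not support that condition. The entry exclusion reaches only patients already known to be hard to follow, not later withdrawals or moves. In Table 1, controls have no study contact between admission and month 6 beyond routine care, and access to the case manager is a feature of the intervention arm.

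For the MLWHFQ there is a second gap. A patient who has died has no 12-month score, and the trial enrols patients aged 75 or over with comorbidity and counts death as a final outcome. The number with a 12-month score will therefore be below 700 by some amount that the Study size section does not consider.

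At stake is how a null result is read. If the trial is described as having 80% power when it has less, absence of a difference will be taken as stronger evidence against the programme than it is.

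**Working it through.** **Inputs.** From the Study size section: control readmission 40% per year, a 20% reduction, 350 per group, alpha 5%, power 80%, no losses; MLWHFQ difference 10 points. Not stated: whether the 20% is relative or absolute, the sidedness of the test, any loss rate, and the MLWHFQ standard deviation (SD). Two-sided testing, the loss rates and the SDs below are assumptions. The normal quantiles are 1.960 (two-sided 5%) and 0.842 (80% power); their sum is 2.802.

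**1. The plan's own figure, no losses.** For two proportions with mean p̄:

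n per group = [1.960·√(2p̄(1−p̄)) + 0.842·√(p1(1−p1)+p2(1−p2))]² / (p1−p2)²

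power = Φ{[|p1−p2|·√n − 1.960·√(2p̄(1−p̄))] / √(p1(1−p1)+p2(1−p2))}

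- **Relative reading, 40% vs 32%.** p̄ = 0.36. The need is 564 per group, not 350. At n = 350: (0.08·√350 − 1.960·0.6788)/0.6765 = (1.497 − 1.330)/0.6765 = 0.246, so power is 59.7%. One-sided, the need is 445 per group and power at 350 is 71.3%.
- **Absolute reading, 40% vs 20%.** The need is 82 per group; power at 350 is above 99.9%.
- **What 350 per group does fit.** A 25% relative reduction (40% vs 30%) needs 356 per group and has 79.3% power at 350. That is not the stated contrast.

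The stated 80% is therefore not reproduced under either reading of "a 20% reduction in hospital admission", even with no losses.

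**2. Effect of losses on readmission power.** Lost patients are first removed entirely, so n = 350·(1−d).

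| Loss d | If 350 per group gave exactly 80% | 40% vs 32% | 40% vs 20% |
|---|---|---|---|
| 0% | 80.0% | 59.7% | >99.9% |
| 5% | 78.0% | 57.5% | >99.9% |
| 10% | 75.7% | 55.3% | >99.9% |
| 20% | 70.7% | 50.5% | >99.9% |

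The first power column is Φ(2.802·√(1−d) − 1.960). For d = 10%: 2.802·0.9487 − 1.960 = 0.698, and Φ(0.698) = 75.7%.

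**3. A milder version.** Cox regression uses follow-up until censoring. If losses were spread evenly over the year, a lost patient would contribute about half a year, so 10% loss would cost roughly 5% of events and 20% loss roughly 10%. From a nominal 80%, that leaves about 78% and 76%. Record review would recover some readmissions and reduce the decline further.

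**4. MLWHFQ.** n per group = 2·SD²·2.802²/10². Setting n = 350 and solving gives SD = 10·√(350/2)/2.802 = 47.2, so 700 patients give exactly 80% only at an SD of about 47. The share that could be missing with 80% power kept is 1 − n/350:

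| Assumed SD | Needed per group | Missing share that still leaves 80% |
|---|---|---|
| 25 | 99 | 72% |
| 30 | 142 | 59% |
| 35 | 193 | 45% |
| 40 | 252 | 28% |
| 47.2 | 350 | 0% |

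Only in the last row does every missing score take power below 80%; there, 20%, 30% or 40% missing would leave about 71%, 65% or 58%.

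**The case against.** The strongest reply is that losses may be few and cheap. Patients who cannot be followed are excluded, deaths come from registries, readmissions can be found in clinical records without contact, and Cox regression keeps partial follow-up. Death is a planned end of follow-up, and it is an event in the analysis of time to readmission or death, so for that analysis it is not a loss. From a nominal 80%, a 5% complete loss costs 2 points. All of this stands, and it makes the table's complete-removal figures close to a worst case. It does not make zero the expected value, and it does not supply an MLWHFQ score for someone who has died.

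Three stronger readings are tempting and not supported:
- **Losses are what make the 80% fail.** No loss rate is given, and the readmission figure already misses 80% on the relative reading and far exceeds it on the absolute one.
- **The MLWHFQ comparison is underpowered.** That needs an SD near 47, which the article does not give. The article says 700 patients also allow this comparison, so the number may exceed what the MLWHFQ needs.
- **Half the patients will die within the year.** The Background states: "Annual mortality exceeds 50% in patients with New York Heart Association (NYHA) classes III and IV". The trial has no NYHA entry criterion, so this figure cannot be taken as its expected mortality.

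**Conclusion.** The point holds in limited form. The Study size section rests its power on zero loss being the expected outcome, which the Discussion undercuts, and the MLWHFQ statement ignores death before month 12.

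For readmission, the size depends on an assumed loss rate and on the scale of the reduction. It is 2 to 9 points for 5% to 20% complete loss if 80% were right, and less with censoring and record review. On the relative reading, 10% loss costs about 4 points on top of a shortfall of about 20 that exists with no loss at all. On the absolute reading it is negligible. The loss assumption is thus secondary to the readmission calculation not reproducing, and a dropout allowance alone would not restore 80% on the relative reading.

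For the MLWHFQ, the missing allowance is clear, but its effect on power cannot be determined until an SD is stated. The correction should be made because the power statement governs how a null result is read, and correcting it is cheap.

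**What to change.** In the Study size section:
1. Delete the clause that presents zero loss as what can be expected, so that the section agrees with the Discussion.
2. State an assumed percentage lost for readmission and, separately, an assumed percentage without a 12-month MLWHFQ score (death plus loss).
3. State whether the 20% reduction is relative or absolute, and give the MLWHFQ SD used. Without these the power cannot be restated.
4. Restate the power for each outcome at the resulting number of evaluable patients or events, keeping 700 patients.

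The change is to wording and calculation only, with no extra patients or visits. The one downside is that the stated power may be less favourable.

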### Statistical analysis

We will first verify the effectiveness of randomisation. The calculated sample size should be sufficient to assure an even balance of the predictors of the outcome variables between the intervention and control groups.

Second, we will estimate the time to readmission or death for each patient, and will obtain curves for time free of such events (Kaplan-Meier method) in the intervention and control groups. These curves will be compared using univariate methods. The effectiveness of DMP will be summarized with hazard ratios (and their 95% confidence intervals) for readmission and mortality obtained by Cox regression, using the hospital as stratification variable. Finally, if the DMP is shown to be effective, we will estimate the number of patients needed to treat (NNT) to prevent one outcome event.

For health-related quality of life, the MLWHFQ score at baseline, 6 months and 12 months will be calculated for each group in the trial. The effect of the DMP on quality of life will be estimated as the difference between groups in the change in MLWHFQ scores during the study. These differences will be accompanied by their respective 95% confidence intervals.

The analyses of the effect of DMP will be performed according to the intention-to-treat principle.

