### Identification of participants, informed consent and randomisation

In each hospital a case manager with a degree in health sciences and special training in HF will identify and register cases admitted for HF each day by reviewing the diagnoses of those aged ≥ 75 years admitted in the acute care unit of the geriatric service. The case manager will then assess each patient and carry out the following activities:

i- Verify the study inclusion and exclusion criteria.

ii- Inform patients (verbally and in writing) and their caregivers (when considered necessary and with the patient's consent) of the characteristics of the DMP and confirm their agreement to participate by asking them to sign the informed consent document.

iii- Assign the patient to the intervention or control group. Randomisation will be conducted independently in each centre. Consecutively numbered envelopes, containing the group to which each patient should be assigned, will be used for this purpose. The envelope will be opened only at the time of patient assignment, to assure concealment of the randomisation list.

iv- Coordinate patient assessment, record the information in the case report form, and transcribe the information to a computerized database.

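### The sample size does not assure balanced outcome predictors, and the readmission and mortality Cox models leave out prognostic variables the trial already collects

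*Protocol article*

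**What the plan says.** The Statistical analysis section begins with a check that randomisation worked and adds: "The calculated sample size should be sufficient to assure an even balance of the predictors of the outcome variables". It then says that the event-free curves will be compared by univariate methods, and that the hazard ratios for readmission and mortality will be "obtained by Cox regression, using the hospital as stratification variable". It names no other covariate for these models.

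The Study size section gives the basis for the number: "700 patients will need to be recruited (350 in each group"), "with an alpha error of 5% and a statistical power of 80" per cent, to detect "a 20% reduction in hospital admission", "under the conservative assumption that the annual frequency of readmission will be 40" per cent. It also assumes that "no patients will be lost to follow-up". The only other justification is a 10-point difference in MLWHFQ. The Design section stratifies randomisation by hospital and by nothing else.

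On timing, the section on identification, consent and randomisation gives step i as "Verify the study inclusion and exclusion criteria". Consent is step ii, opening the envelope step iii, and patient assessment with entry in the case report form step iv.

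**The concern.** A size chosen for power against a readmission difference has no built-in balance property, so the sentence credits the design with something it does not deliver. A reader may take from it that baseline predictors need no place in the analysis.

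The document itself treats such predictors as important. The Background links advanced age to hospitalisation and death, and the Discussion ranks comorbidity at least level with heart failure as a prognostic factor. In a Cox model, leaving out strong predictors pulls the estimated hazard ratio towards 1 and lowers power. What is at stake is efficiency for readmission and mortality. The validity of the planned test is not in question, and the MLWHFQ analysis is outside this point.

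**Working it through.** **Inputs from the protocol.** 350 per group; control risk of readmission 40% at 12 months; 20% reduction, read as relative (32%); alpha 5%, taken as two-sided because the side is not stated; no loss to follow-up; eight hospitals as strata.

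**Assumed input.** The prognostic strength of the covariates, expressed as the hazard ratio per SD of their combined score. The documents give no figure.

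**1. The plan's own figure.** For two proportions with pooled variance under the null:

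n per group = [1.960·√(2·0.36·0.64) + 0.842·√(0.40·0.60 + 0.32·0.68)]² / 0.08² = (1.330 + 0.569)² / 0.0064 ≈ 564.

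The stated 350 is not reproduced. Power at 350 per group is Φ[(0.08·√350 − 1.330)/0.676] = Φ(0.246) = 59.7%. On the hazard scale, HR = ln 0.68 / ln 0.60 = 0.755 and events = 350·0.40 + 350·0.32 = 252. Power is then Φ(√252·0.281/2 − 1.960) = Φ(0.271) = 60.7%. The baseline for any gain is therefore about 60%, not 80%.

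**2. Balance at 350 per group.** For a predictor with 50% prevalence, SE = √(2·0.5·0.5/350) = 0.0378. A gap of 5 points is 0.05/0.0378 = 1.32 SE, so P(gap ≥ 5 points) = 18.6%.

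On the standardised scale, SE = √(2/350) = 0.0756. P(|d| > 0.10) = 18.6% and P(|d| > 0.20) = 0.8%. If ten predictors were independent, the chance that at least one exceeds 0.10 would be 1 − (1 − 0.186)^10 = 87%. The trial's comorbidity measures overlap, so this last figure is only illustrative.

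**3. Power gain for readmission.** Simulation: 700 patients, eight strata, exponential times, a normally distributed prognostic score, 12-month risks held at 40% and 32%, stratified Cox Wald test at two-sided 5%, 1,500 trials per row.

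| HR per SD (log-hazard SD) | Hospital strata only | Plus score | Gain, points |
|---|---|---|---|
| 1.35 (0.3) | 62.2% | 63.4% | 1.2 |
| 1.65 (0.5) | 61.1% | 65.0% | 3.9 |
| 2.01 (0.7) | 60.5% | 68.0% | 7.5 |
| 2.46 (0.9) | 59.3% | 72.0% | 12.7 |
| 3.00 (1.1) | 59.1% | 79.3% | 20.2 |

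The simulation error of a single power near 60% is √(0.6·0.4/1500) = 1.3 points. A separate set of 1,500 trials gave gains of 4.9 points at SD 0.5 and 8.6 at SD 0.7, about one point higher than above.

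**4. Cross-check by formula.** Replacing 252 events by 252/(1 − R²) in the hazard-scale formula gives 62.9%, 65.2% and 70.3% for R² of 0.05, 0.10 and 0.20. The gains are 2.2, 4.6 and 9.7 points. R² is also an assumption.

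**5. Which covariates are safe.** Eligibility is checked at step i, but a patient needs only one comorbidity criterion. Someone who qualifies on number of drugs need not have had a Charlson score or ADL count completed by then. Full assessment is step iv, after the envelope, and Table 1 lists the baseline variables after randomisation. Age and emergency hospitalisation in the previous 3 months are historical facts that allocation cannot change. Charlson and ADL values are not shown to be fixed before allocation.

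**The case against.** The best defence is that the planned analysis is correct as it stands. It follows intention to treat, and its stratification matches the randomisation. Chance imbalance under valid randomisation is already reflected in the type I error and the confidence interval. The balance sentence is worded as an expectation, and severe imbalance is indeed unlikely. A covariate list is also commonly left to a statistical analysis plan, which is not shown. The adjusted hazard ratio answers a slightly different, conditional question: at HR per SD 2.01 the simulated average was 0.731 adjusted and 0.753 with hospital strata only.

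Most of this stands. It removes any charge of bias or invalidity and makes adjustment a matter of efficiency. It does not rescue the balance sentence, which credits the sample size with a property that it lacks. Nor does it make the stated model the better choice, since the article names that model and the variables are already collected.

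A reader might also infer that covariates were left out because balance was thought assured, or that the balance check decides the analysis. The text says neither; the sentences merely stand in the same section.

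**Conclusion.** The point holds as a modest, worthwhile improvement. The sample size does not assure even balance: a 5-point gap in a predictor with 50% prevalence arises by chance in 18.6% of trials of this size, although a standardised difference above 0.20 arises in only 0.8%. Adjusting the readmission model would add roughly 1 to 8 points of power for weak to moderately strong predictors (HR per SD 1.35 to 2.0), and more beyond that.

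This range rests on the assumed strength, on the relative reading of the 20% reduction, on a two-sided test, and on a simulation in which the score is fully known. It should not be narrowed to a single figure.

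Three stronger conclusions are tempting but unsupported:
- The hospital-only estimate is not biased by chance imbalance.
- No gain can be stated for mortality, because the protocol gives no mortality rate for the trial.
- Adjustment does not bring the trial to 80% power. At HR per SD 2.01 it reaches 68.0%, and the shortfall in the sample size calculation is a separate and larger matter.

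**What to change.** Delete the sentence saying that the sample size assures balance. State that the main Cox models for readmission and for mortality are stratified by hospital and adjusted for a short fixed list whose values cannot depend on allocation: age and emergency hospitalisation in the last 3 months. Add Charlson index and ADL dependence provided their values are recorded before the envelope is opened. Report the model with hospital strata only as a sensitivity analysis.

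The cost is small: a sentence in the analysis section and no new variables. There are three practical consequences. Charlson and ADL scoring has to be completed and recorded before step iii. The adjusted hazard ratio must be labelled as conditional on the covariates. A simple rule is needed for the few missing covariate values.

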## Methods/Design

### Design

The HF-GERIATRICS study is a trial in elderly patients who are admitted with a primary diagnosis of HF in acute care units of eight geriatric services in Spain. Patients are assigned randomly to a DMP (intervention group) or to receive usual care (control group). Randomisation is stratified by hospital and is conducted with concealment of the randomisation list. The two trial groups are followed for 12 months.

The project has been approved by the clinical research ethics committee of all participating hospitals (Comité de Etica y Ensayos Clínicos (CEIC) de Galicia, CEIC del Complejo Hospitalario de Caceres, CEIC del Hospital Universitario La Paz, CEIC del Complejo Universitario de Albacete, CEIC del Hospital Universitario de Guadalajara, CEIC del Hospital Central de Asturias, CEIC del Hospital Universitario de Getafe, CEIC del Hospital Universitario de San Carlos, Spain).

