Number of emergency department visits	^#^To be detected by review of the computerized clinical history or by the hospital admission records, counting all episodes after the date of discharge of the index admission. The number of these visits directly related with heart failure will be recorded.
Intermediate outcome variables	^#^Knowledge of disease ^#^Self-care measures
Final outcome variables	^#^Readmission.- all hospitalisation episodes of more than 24 hours following the date of discharge of the index admission. The following variables will be recorded: number and proportion of patients who are readmitted, number of readmissions per patient, and length of hospital stay during readmissions. ^#^Death.- To be determined by follow-up of each patient. This will be documented in the clinical history and the mortality registries. ^#^Quality of life.- Measured by the Minnesota Living With Heart Failure Questionnaire

ADLs: Basic activities of daily living; IADLs: Instrumental activities of daily living; * Variables to be registered only during the index admission; # Variables to be registered at the index admission and at 6 and 12 months.

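### The quality-of-life effect is planned as a difference in MLWHFQ change with no baseline or hospital adjustment named; adding both would gain precision at no cost

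*Protocol article*

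**What the plan says.** The quality-of-life paragraph of Statistical analysis first describes the scores: "the MLWHFQ score at baseline, 6 months and 12 months will be calculated for each group in the trial". It then fixes the effect measure: "The effect of the DMP on quality of life will be estimated as the difference between groups in the change in MLWHFQ scores", accompanied by 95% confidence intervals. No covariate appears in that paragraph.

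The two candidate covariates are available:

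- **Baseline score.** Table 2 (Study variables) gives the MLWHFQ the mark explained as "Variables to be registered at the index admission and at 6 and 12 months".
- **Hospital.** The Design section says "Randomisation is stratified by hospital". The readmission and mortality hazard ratios are to be "obtained by Cox regression, using the hospital as stratification variable".

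So the design's stratification factor is named in the analysis of two main outcomes and not in that of the third.

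**The concern.** A simple difference in change subtracts the whole baseline score from the follow-up score, which fixes the baseline slope at 1. Here baseline is taken during an acute admission for heart failure and follow-up comes 6 and 12 months later. A low to moderate correlation is therefore plausible, although the article does not report one. If the true slope is below 1, the subtraction adds noise and over-corrects chance differences at baseline. A model that estimates the slope avoids this.

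Leaving hospital out has a smaller effect. To the extent that allocation is balanced within hospitals, an analysis that ignores hospital counts between-hospital variation as error and reports a wider interval than it needs to.

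At stake is the width of the confidence interval for a main outcome, and power for effects below the 10-point target. The validity of the comparison is not at stake.

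**Working it through.** **Inputs from the article:** 350 patients per arm; 10-point MLWHFQ difference; control mean 50; alpha 5% (taken as two-sided); power 80%; no loss to follow-up (all Study size).

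**Inputs not given, so assumed:** the SD of the MLWHFQ; the correlation ρ between baseline and follow-up; the ratio k of follow-up SD to baseline SD; the share of variance due to hospital.

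**1. The plan's own figure.** The MLWHFQ sample-size statement cannot be reproduced, because no SD is given. The SD at which 350 per arm gives exactly 80% power for 10 points is 10 / [(1.960 + 0.842) × √(2/350)] = 10 / (2.802 × 0.0756) = 47.2. With assumed SDs of 20, 25 and 30, the number needed is 63, 99 and 142 per arm, and 350 per arm gives over 99% power in each case.

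**2. The two estimators.** Let the baseline SD be σ and the follow-up SD kσ. In large samples with 1:1 allocation, the variance of the treatment effect is proportional to:

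- change score: σ²(k² + 1 − 2ρk)
- baseline-adjusted: σ²k²(1 − ρ²)

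The first minus the second is σ²(1 − ρk)², which is never negative. The adjusted estimator is therefore never less precise, and the two are equal only when the slope ρk is 1. When ρk is below 0.5, the change score is noisier even than comparing follow-up scores alone, because k² + 1 − 2ρk then exceeds k².

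**3. Equal SDs (k = 1).** The variance ratio is (1 − ρ²) / [2(1 − ρ)] = (1 + ρ)/2, so the reduction is (1 − ρ)/2. The interval narrows by the factor √[(1 + ρ)/2]. The half-widths below take an assumed SD of 25 and scores from all 350 per arm: 1.96 × 25 × √(2/350) = 3.70, multiplied by √[2(1 − ρ)] for change or √(1 − ρ²) for adjusted.

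| Assumed ρ | Variance reduction | CI width factor | Half-width, change | Half-width, adjusted |
|---|---|---|---|---|
| 0.2 | 40% | 0.775 | 4.69 | 3.63 |
| 0.3 | 35% | 0.806 | 4.38 | 3.53 |
| 0.5 | 25% | 0.866 | 3.70 | 3.21 |
| 0.7 | 15% | 0.922 | 2.87 | 2.65 |
| 0.8 | 10% | 0.949 | 2.34 | 2.22 |

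**4. Unequal SDs.** At ρ = 0.7 and k = 1.2, the change term is 1.44 + 1 − 1.68 = 0.760 and the adjusted term is 1.44 × 0.51 = 0.734, a reduction of about 3%. At ρ = 0.7 and k = 0.8, the terms are 0.520 and 0.326, a reduction of 37%. At ρ = 0.5 the reduction runs from 43% (k = 0.8) to 13% (k = 1.2).

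**5. Hospital.** The article gives no between-hospital variance. As an illustration only, if hospital explained a further 1% to 5% of variance, the 25% reduction at ρ = 0.5 would become 1 − 0.75 × 0.99 = 26% to 1 − 0.75 × 0.95 = 29%.

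**6. A smaller effect.** For an assumed 5-point difference with SD 25 and k = 1, power at 350 per arm (change score against adjusted) is 61% against 79% at ρ = 0.3, 75% against 86% at ρ = 0.5, and 93% against 96% at ρ = 0.7.

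**The case against.** The strongest objection is that the article does not call the analysis unadjusted. A linear model of change with baseline as covariate also estimates a difference in change, and gives the same treatment coefficient as a model of the follow-up score with baseline as covariate. Covariate lists are commonly left to a fuller document, which may exist. This stands in part: a reader might infer that the plan rules out adjustment, and it does not. But the article does state an effect measure, read plainly it is a difference in mean change, and the one covariate it names is attached only to the Cox regression. Improving that sentence is not the same as faulting an omission.

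Three stronger readings are tempting and are not supported:

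- **Bias.** A difference in change is unbiased under randomisation, and its confidence interval already reflects chance baseline imbalance.
- **A fixed, large saving.** The size depends on ρ and on the two SDs, none of which the article reports.
- **Too few patients for quality of life.** The 700 is derived from readmission, and the 10-point claim is an added remark. Under assumed SDs of 20 to 30, power for 10 points is already above 99%. Even a change score with SD 25 and ρ = 0.3 needs only 138 per arm for 10 points, against 90 with adjustment.

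Ample power under those SDs limits how much the point matters but does not remove it. The SDs are assumptions, the article claims only 80%, and the planned result is an interval whose width depends on the estimator.

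**Conclusion.** The point holds as a free improvement. The planned MLWHFQ estimator is valid, but less precise than the collected data allow. With equal SDs, baseline adjustment reduces the variance by (1 − ρ)/2, about 10% to 40% for an assumed ρ of 0.8 down to 0.2, which narrows the interval by about 5% to 23%. With unequal SDs the gain can be larger or close to nil (about 3% in one case above). Hospital adds an unquantified and probably small amount, and including it would make the quality-of-life analysis consistent with the stratified design and the Cox regression.

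That adjustment does not lose precision is a large-sample result for 1:1 allocation and does not depend on ρ; only the size of the gain does. Both estimators require that the baseline score is not influenced by allocation. At the 10-point target the practical benefit is probably a narrower interval. The benefit in power arises for smaller effects.

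**What to change.** Replace the sentence that defines the quality-of-life effect with wording such as:

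> The effect of the programme on quality of life at 6 and at 12 months is the adjusted between-group difference in mean MLWHFQ score, with its 95% confidence interval. Both estimates come from one linear repeated-measures model of the 6- and 12-month scores, with treatment, time, treatment-by-time, baseline MLWHFQ, baseline-by-time and hospital as terms. Mean changes from baseline by group are descriptive.

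This keeps both time points and leaves no choice of model to be made after the data are seen. It costs one passage of analysis wording and uses only variables already recorded. It should be fixed before outcomes are compared by group, since adjustment chosen later is open to challenge. If a full analysis plan already specifies such a model, the article's sentence need only be brought into line with it.
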